#### Missing data and adherence

Participants missing ≥ 10% of required sleep intervention nights (defined as < 22 nights of wearing the sleep intervention over the 8-week intervention period) will be flagged for sensitivity analyses. If a participant misses > 2 consecutive weeks of data and/or fails to complete either of the full-length, digital cognitive assessments, such participants will be excluded from per-protocol analyses but retained in intention-to-treat models. Multiple imputations will not be applied due to the small sample size; instead, pattern mixture modeling or last observation carried forward (LOCF) methods will be used where applicable.

Adherence to the recommended neuromodulation utilization for the sleep intervention will be monitored via the Elemind application, which will log device usage and track sleep metrics. In addition, weekly phone or video check-ins (10–15 minutes) will be made to monitor engagement, support adherence, and troubleshoot technical issues. All reports of adherence will be documented upon the completion of each call/video check-in.

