### Statistical analysis plan

#### Power and sample size considerations

This trial is designed to be an exploratory, hypothesis-generating randomized controlled trial. Given the exploratory nature of this three-arm trial, a sample size of 60 participants (20 per group) was selected for this trial to balance feasibility with the ability to detect preliminary signals across intervention arms. Power analyses were conducted via simulation for linear mixed-effects models (LMMs) using estimated parameters relevant to repeated cognitive and biomarker outcomes measured at two time points (baseline (week 0) and 8 weeks). Assuming a moderate effect size (Cohen’s *f*^2^ = 0.25), *α* = 0.05, a compound symmetry covariance structure, and no attrition, this sample size yields approximately 60–65% power to detect a significant group × time interaction. While this power is modest, it is sufficient to estimate effect sizes with reasonable precision and assess trends across intervention arms. Since LMMs maximize available data and accommodate unbalanced designs and missing data, LMMs are preferred over repeated measures ANOVA for small-sample trials with incomplete follow-up. Results from this study will guide power calculations and design refinements for a fully powered randomized controlled trial. As generally recommended for early-phase behavioral intervention studies, this trial’s emphasis will be placed on effect sizes and confidence intervals instead of solely statistical significance.

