Primary group comparisons will be conducted using LMMs, which offer flexibility for handling repeated measures, unbalanced data, and missingness under the Missing at Random assumption. Each LMM will include fixed effects for group (sleep, exercise, combined sleep + exercise), time (baseline, 8-week follow-up), and the interaction term between group × time. Subject-specific random intercepts will be included to account for intra-individual correlation over time. The main test of intervention efficacy will be the group × time interaction term. To evaluate whether improvements in biomarkers (e.g., HbA1c, hs-CRP) moderate the effects of the interventions on cognitive outcomes, exploratory moderation models will be conducted. These models will include biomarker change scores, group assignment, and group × biomarker interaction terms as predictors of cognitive change. Moderation models will use PROCESS v5.0 Macro for SPSS with bias-corrected bootstrapping (5,000 resamples). Significant interactions will be probed using Johnson-Neyman techniques.

Given the small sample size, power for detecting small effects will be limited. Thus, all models will report estimated effect sizes (Cohen’s *d*, partial *η*^2^), 95% confidence intervals, and significance levels (*α* = 0.05). No corrections for multiple comparisons will be applied to primary outcomes; however, for secondary and exploratory outcomes, a Benjamini–Hochberg false discovery rate (FDR) correction will be used to control for Type I error. Composite indices may be created to reduce variable dimensionality. For cognitive outcomes, domain-specific cognitive function scores will be z-scored and aggregated into a global composite score. For blood-based biomarkers, z-scored values will be averaged to create an overall plasma-based AD risk index as well as a cardiometabolic risk index for all subjects.

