Missing data will be handled using maximum likelihood estimation within LMMs. For summary scores or self-report questionnaires with partially missing responses, scale-specific rules will be applied, if available. Participants missing more than 2 weeks of intervention or follow-up cognitive assessments will be excluded from per-protocol models but retained in intention-to-treat analyses. Missingness patterns will be analyzed and classified as Missing Completely at Random (MCAR), Missing at Random (MAR), or Missing Not at Random (MNAR). All assumptions for normality, linearity, and homoscedasticity will be checked using residual plots and Kolmogorov–Smirnov tests. Skewed variables (e.g., hs-CRP) will be square root- or log-transformed prior to modeling. Outliers will be identified using leverage and Cook’s distance, and sensitivity analyses will be performed with and without influential points.

As an alternative analytic strategy, if models fail to yield significant results due to insufficient power or high variability, effect sizes and confidence intervals (CIs) will be emphasized. A simplified analysis approach using ANCOVA (controlling for baseline scores) will be explored for key outcomes. Lastly, pattern mixture modeling may be used to examine intervention effects under different missing data assumptions.

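### The plan promises to label missingness as MCAR, MAR or MNAR, but observed data cannot separate MAR from MNAR, and the one analysis that could relax MAR is optional or replaceable by LOCF

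*Protocol article*

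**What the plan says.** The *Analysis plan* compares groups with linear mixed models at two time points, baseline and week 8. It describes these models as dealing with "missingness under the Missing at Random assumption" and adds: "Missing data will be handled using maximum likelihood estimation within LMMs". It then commits to a classification step: "Missingness patterns will be analyzed and classified as Missing Completely at Random (MCAR), Missing at Random (MAR), or Missing Not at Random (MNAR". No method for the classification is named. In a later paragraph on alternative strategies it says that "pattern mixture modeling may be used to examine intervention effects under different missing data assumptions".

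A second statement is under *Missing data and adherence*, within the description of the sleep-only arm. It rules out one approach, "Multiple imputations will not be applied due to the small sample size", and puts another in its place: "pattern mixture modeling or last observation carried forward (LOCF) methods will be used where applicable". The article does not say whether this rule extends to the other two arms.

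The power section plans for "a sample size of 60 participants (20 per group") and assumes "a compound symmetry covariance structure, and no attrition". No expected dropout rate appears anywhere.

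**The concern.** MAR and MNAR differ only in whether, given what was observed, missingness still depends on the values that were not observed. The collected data carry no information on that. The plan therefore commits to a three-way result of which only one part, evidence against MCAR, can be obtained. If the report says that missingness was classified as MAR, readers may take the assumption behind the main model as checked.

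This matters more because nothing else in the document guarantees a check. One statement makes pattern mixture modelling optional. The other is satisfied by LOCF alone.

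Dropout related to arm is plausible on the document's own facts. Participants are not blinded and there is no sham. The exercise and combined arms attend two supervised sessions a week. The sleep-only arm is home-based and may do its week-8 cognitive testing and surveys by video. The combined arm's cumulative burden is acknowledged. The trial stresses effect sizes and intervals and is meant to inform the power calculation of a later trial, so a biased estimate could be carried forward.

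**Working it through.** There is no figure in the plan to reproduce. The point rests on identifiability and on comparing two sections.

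**1. Why MAR and MNAR cannot be separated.** For one arm, let *d* be the share without a week-8 value, *m_C* the completers' week-8 mean, and *m_MAR* the mean that the model predicts for dropouts from observed data. Write the dropouts' true mean as *m_MAR* + δ. Then

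arm mean = (1 − *d*) × *m_C* + *d* × (*m_MAR* + δ).

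MAR implies δ = 0; a non-zero δ is MNAR. The observed data are the baseline values, who dropped out, and the completers' week-8 values. None of these involves δ, so every δ fits the data equally well. A link between dropout and an observed baseline variable is evidence against MCAR, but says nothing about δ.

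**2. What the two sections commit to.**

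| | *Analysis plan* | *Missing data and adherence* (sleep-only) |
|---|---|---|
| Main handling | Maximum likelihood in the mixed model, under MAR | Pattern mixture or LOCF, where applicable |
| Analysis that could relax MAR | Pattern mixture, optional | Pattern mixture, replaceable by LOCF |

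For the full-length cognitive assessments and the blood markers measured twice, the only value before week 8 is baseline. LOCF then gives week 8 = baseline, so change = 0 for every dropout. That is one strong assumption, not a range of departures from MAR. If used only in the sleep-only arm, it would also handle dropouts differently by arm.

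**3. Size, as an illustration.** Dropout rates and shifts are assumptions; the documents give neither.

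- Error in one arm's mean = *d* × δ. Low: 0.2 × 0.3 = 0.06 SD. High: 0.3 × 0.5 = 0.15 SD.
- Error in a between-arm contrast = *d*₁δ₁ − *d*₂δ₂. With 30% v 10% and a 0.5 SD shift in both: 0.15 − 0.05 = 0.10 SD. With equal dropout and equal shift: 0.

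For scale, with 20 per arm, no dropout, unit SD and an assumed baseline-to-week-8 correlation of 0.5, the SD of change is √(2 × (1 − 0.5)) = 1. The 95% half-width for a difference in change between two arms is then about 2.0 × √(2/20) = 0.63 SD. So 0.06 to 0.15 SD is about 10% to 24% of the half-width (0.06/0.63 and 0.15/0.63).

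**4. Effect on a test.** A simulation of two arms of 20 (4,000 runs per scenario, baseline-adjusted comparison, correlation 0.5, no true difference) gave:

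| Dropout, arm 1 v arm 2 | Shift in dropouts | Bias in contrast | Type I error (nominal 5%) |
|---|---|---|---|
| 10% v 10% | −0.8 SD | 0.00 SD | 5.2% |
| 10% v 30% | −0.8 SD | 0.16 SD | 7.9% |
| 5% v 30% | −1.0 SD | 0.25 SD | 12.2% |

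The biases agree with the formula: 0.3 × 0.8 − 0.1 × 0.8 = 0.16 and 0.3 × 1.0 − 0.05 × 1.0 = 0.25. The last two rows use shifts of 0.8 and 1.0 SD, larger than the 0.3 to 0.5 SD above, and show a less favourable case.

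**The case against.** The strongest defence is that no estimate depends on the label. The main analysis is fixed in advance, and no sentence changes the method according to the classification. That stands. A reader might infer that the classification decides whether pattern mixture modelling is run, but the two sentences are in separate paragraphs and nothing links them. The harm is in how the result may be reported and read.

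Second, part of the step is sound: examining missingness patterns is useful, and data can contradict MCAR. That also stands. It would be too strong to say that the data reveal nothing about the mechanism; only the MAR/MNAR split is impossible.

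Third, the plan names pattern mixture modelling twice, and details such as the shift range commonly belong in a statistical analysis plan that is not shown. The absence of those details is no fault here. What remains is in the stated text: one section makes the analysis optional, and the other lets LOCF stand in for it and disagrees with the maximum-likelihood rule.

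Fourth, the size is hypothetical and modest against the precision of 20 per arm, and it cancels when arms lose similar participants at similar rates. This is correct and limits the weight of the point.

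**Conclusion.** The point holds in a limited form. The classification cannot be carried out as stated, because MAR and MNAR are indistinguishable from observed data. The plan does not commit to any analysis that relaxes MAR, and its two statements on missing data disagree.

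The illustrative size is 0.06 to 0.15 SD in one arm's mean, resting on assumed dropout of 20% to 30% and an assumed shift of 0.3 to 0.5 SD. This should not be read as an expected bias in the group × time contrast. That bias depends on the difference between arms in dropout share times shift, and is zero if these products are equal. Nor do the documents support saying that informative dropout will go untested: pattern mixture modelling is allowed, just not assured.

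For an exploratory, hypothesis-generating pilot, this is a desirable correction rather than one on which the trial's validity turns.

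**What to change.** 1. Delete the MCAR/MAR/MNAR classification. Report instead the amount of missing data by arm and outcome, and its association with baseline variables.
2. Keep the maximum-likelihood mixed model under MAR as the primary analysis in all three arms, and call MAR an assumption.
3. Remove LOCF, and reconcile *Missing data and adherence* with the *Analysis plan* so that one rule covers every arm.
4. Replace the optional pattern mixture analysis with a committed delta-shift analysis for the primary cognitive outcomes and NfL. Vary the shift separately by arm over a range fixed before outcome data are seen, for example 0 to 0.5 SD in the unfavourable direction: lower for cognition, higher for NfL. Report the shift, if any, at which the conclusion changes. A single negative range for all outcomes would not do, since for NfL it would make dropouts look better.

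The exclusion of multiple imputation is no obstacle. With two time points the shifted contrast is the model's contrast plus *d*₁δ₁ − *d*₂δ₂ (δ signed on the outcome scale), with a small addition to the variance because the dropout shares are estimated. The cost is a few sentences of plan wording and light programming, with no change to data collection or sample size.

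### The more precise baseline-adjusted analysis sits as an unfixed fallback beside a significance condition, and the LOCF and per-protocol rules conflict with those in the analysis plan

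*Protocol article*

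**What the plan says.** The Analysis plan section of the protocol article fixes the primary method in advance: "Primary group comparisons will be conducted using LMMs", and "The main test of intervention efficacy will be the group × time interaction term". The time factor has two levels, baseline and week 8, and each participant has a random intercept. On multiplicity it says "No corrections for multiple comparisons will be applied to primary outcomes".

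The last paragraph of the same section sets out an alternative strategy. It begins with a condition: "if models fail to yield significant results due to insufficient power or high variability, effect sizes and confidence intervals (CIs) will be emphasized". The next sentence reads "A simplified analysis approach using ANCOVA (controlling for baseline scores) will be explored for key outcomes". The key outcomes are not named, and ANCOVA appears nowhere else in the article.

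Missing data are covered twice:
- In the Analysis plan: "Missing data will be handled using maximum likelihood estimation within LMMs", with the option that "pattern mixture modeling may be used to examine intervention effects under different missing data assumptions".
- Under Missing data and adherence, in the sleep-only arm, multiple imputation is ruled out and "instead, pattern mixture modeling or last observation carried forward (LOCF) methods will be used where applicable".

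Per-protocol exclusion is also covered twice. The sleep-only section counts more than two consecutive weeks of missing data, or failure to complete either full-length cognitive assessment. The Analysis plan counts more than two weeks of missed intervention or follow-up cognitive assessments, with no requirement that they be consecutive.

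**The concern.** Three things are left open that should be settled before any data are seen.

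First, the trial calls its own power modest, yet its main test ignores information that it already collects. Adjusting for the baseline value of the outcome is the more precise analysis in a randomised comparison with one follow-up. The plan mentions that adjustment only as something to explore.

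Second, ANCOVA stands in a paragraph that opens with non-significance, with no fixed role and no named outcomes. If it is then read as evidence of efficacy, each outcome has two routes to p < 0.05. The primary list holds nine biomarkers as well as the cognitive scores, all without multiplicity correction, so any inflation repeats across many outcomes.

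Third, LOCF and maximum likelihood rest on different assumptions and can give different arm contrasts. No order of precedence is given. The combined arm carries the greatest burden, which the article itself plans to manage, so unequal dropout is a realistic prospect. The results are meant to guide the power calculations of a larger trial, so bias or lost precision would carry forward.

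**Working it through.** **Inputs from the article.** 60 participants, 20 per arm; α = 0.05; outcomes at weeks 0 and 8; compound symmetry; no attrition; stated power 60–65% at f² = 0.25 (Power and sample size considerations). The article gives no within-person correlation ρ, dropout rate or expected common gain. The values used for these below are assumptions.

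**The plan's own power figure.** A noncentral F with 2 and 57 degrees of freedom and λ = f²N = 0.25 × 60 = 15 gives 93.2%. Reading 0.25 as f gives λ = 0.0625 × 60 = 3.75 and 37.4%. One way to reach 60–65% is f = 0.25 on the raw SD scale, λ = 3.75/[2(1−ρ)], with ρ about 0.71–0.74. Because ρ is not stated, the figure can be neither confirmed nor refuted, and this point does not depend on it. Taken at face value, 60–65% power means the non-significance condition is met 35–40% of the time per outcome when the assumed effect is real. With no effect it is met 95% of the time.

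**Step 1: what the main test is.** With two visits and complete data, the group × time test from a random-intercept model equals a one-way ANOVA of change scores. On the unit-SD scale:
- variance of change = 2(1−ρ)
- residual variance of ANCOVA = 1−ρ²
- ratio = (1−ρ²)/[2(1−ρ)] = (1+ρ)/2

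**Step 2: the precision forgone.** Assume one arm is 0.8 SD better than the other two. The between-arm sum of squares is 20 × [2 × (0.8/3)² + (1.6/3)²] = 8.53. Dividing it by each variance gives λ, and the noncentral F (2 and 57 df for change, 2 and 56 for ANCOVA) gives power. Simulation agrees to within about a point.

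| Assumed ρ | Variance ratio | λ change → ANCOVA | Power change → ANCOVA |
|---|---|---|---|
| 0.3 | 0.65 | 6.10 → 9.38 | 57% → 76% |
| 0.5 | 0.75 | 8.53 → 11.38 | 72% → 84% |
| 0.7 | 0.85 | 14.22 → 16.73 | 92% → 95% |

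**Step 3: two tests of one hypothesis.** Null simulation, 20 per arm, 100,000 runs per ρ. Each test alone rejects about 5% of the time. Rejection by either test, which is the same as running ANCOVA after a non-significant interaction:

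| Assumed ρ | 0.3 | 0.5 | 0.7 | 0.8 | 0.9 |
|---|---|---|---|---|---|
| Type I error per outcome | 7.7% | 7.5% | 7.0% | 6.6% | 6.2% |

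**Step 4: LOCF on outcomes seen only at weeks 0 and 8.** The last observation before a missing week 8 is the baseline, so the imputed change is zero. Mean change under LOCF = (1 − dropout) × true change. With an equal true gain of 0.5 SD in two arms and 5% versus 25% dropout:
- 0.95 × 0.5 = 0.475 SD
- 0.75 × 0.5 = 0.375 SD
- false difference = 0.10 SD

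In a three-arm simulation with 10/10/30% dropout and the same common gain, LOCF analyses (ρ 0.5 and 0.7) rejected a true null 6.3–7.1% of the time. With equal dropout in all arms, or no common gain, they stayed near 5%.

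**Step 5: the two per-protocol rules.** Take a participant who misses three separate, non-adjacent weeks and completes both full-length assessments. The sleep-only rule keeps this person and the Analysis plan rule excludes them.

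**The case against.** The strongest reply is that the primary estimator is settled. The mixed model and its interaction term are named beforehand and nothing later replaces them. A reader might infer that the primary estimator depends on the result, or that ANCOVA is run only when the mixed model fails. The article does not say so. What non-significance expressly triggers is a reporting emphasis, and the ANCOVA sentence carries no condition of its own. The link is an inference from the order of the paragraph. This stands, and the inflation in Step 3 applies only if ANCOVA is treated as a second efficacy test.

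A reader might also infer that LOCF is prescribed for the primary outcomes and that every dropout will count as zero change. That goes too far as well. LOCF is one of two options, allowed where applicable, in the section for one arm and beside rules on headband nights. Nightly sleep data and twice-weekly cognitive pulses do have later observations to carry forward. Zero change follows only for outcomes measured solely at weeks 0 and 8.

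The trial is openly exploratory, promises no trial-wide 5% error rate, and already undertakes to report effect sizes and intervals for all models. The per-protocol analysis is not called primary, and both rules keep those excluded in intention-to-treat. These facts lower the severity.

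It may further be said that choosing the mixed model over ANCOVA is a matter of taste. That does not hold: the baseline is already measured, and adjusting for it costs nothing in a randomised comparison. The gain does require arms analysed as randomised. Screening and consent permits reassignment on baseline sleep and activity, so this condition has to be written in.

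**Conclusion.** The concern holds as a should-fix for an exploratory pilot. The named main test is valid but less precise than the baseline-adjusted analysis that the plan leaves to exploration: ANCOVA has 0.65 to 0.85 of its variance for assumed ρ of 0.3 to 0.7, provided randomisation is preserved. ANCOVA's role and outcomes are not fixed and it is placed under a condition on significance. Used as a second test, it adds about 1 to 3 percentage points to the 5% error per outcome. The condition also sits badly with the article's own commitment to effect sizes and intervals whatever the result.

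The two missing-data statements have no hierarchy. Read for one arm, the sleep-only rule treats that arm differently; read for the whole trial, it competes with maximum likelihood. For week 0 and week 8 outcomes the possible bias is about 0.10 SD under the assumed gain and dropout, and it vanishes if dropout is equal or there is no common gain. The per-protocol mismatch is real but minor.

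**What to change.** - Make one baseline-adjusted model primary for every week 0/8 outcome, whatever the result: either ANCOVA of week 8 on baseline, or a likelihood-based mixed model with a common baseline mean across arms. The second keeps the planned maximum likelihood handling of missing data.
- State that participants are analysed in the arm to which they were randomised.
- Remove the condition on significance and report effect sizes and confidence intervals for all outcomes, as the article already promises elsewhere.
- Delete LOCF for outcomes measured only at weeks 0 and 8, and keep pattern-mixture modelling as the missing-data sensitivity analysis. If LOCF is wanted for nightly or twice-weekly series, say for which and in what role.
- Adopt one per-protocol definition for all arms, stating whether missed weeks must be consecutive and which assessments count.

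The cost is wording in the analysis plan, settled before data are seen. No extra participants, visits or measurements are needed.
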